#### Exit Interview

Following completion of the 12-week protocol, baseline and discharge surveys, TSST-OL, and 30s-STS, the participants are invited to complete a semistructured exit interview to garner feedback regarding the feasibility, acceptability, and appropriateness of the captured data. The participants also complete the Theoretical Framework of Acceptability (TFA) [42] and Net Promoter Score (NPS) [43] surveys. Feedback from the exit interview, TFA, and NPS is incorporated into the ongoing study procedures as appropriate and is particularly important for future applications of this work, specifically as a guide for implementation and validation of the digital biosignature (Phase 2).

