The nearly ubiquitous consumer adoption of health care technology—particularly wearables [15,16]—presents a promising solution for improved comprehensive monitoring of the pain experience, with opportunities for personalized medicine approaches [17,18]. Unlike self-reports, wearables provide longitudinal and objective measures of health that reflect real-time fluctuations inherent to the pain experience. Wearables also present a unique opportunity for collecting multiple biomarkers (eg, heart rate and sleep data) that can be combined with other domains to inform the development of biosignatures. Through machine learning and related analytic techniques, several digital biosignatures of human health have already been developed using data from wearable technology [17,19,20].

In summary, mechanisms underlying the persistence of chronic pain in youth remain poorly understood. Multisystem involvement (eg, autonomic, sensory, immune) and frequent symptom fluctuations complicate the reliability of traditional self-report monitoring techniques and create barriers to individualized clinical decision-making. Therefore, the purpose of this study, named Targeted Real-Time Assessment of Chronic Pain (TRAC-Pain), is to overcome the limitations of the current standards for pain monitoring through the development of a digital biosignature using consumer-available wearable technology. The expected result will be a digital biosignature of the pain experience in youth with chronic MSK pain. The secondary aim of this study is to assess the feasibility, acceptability, and appropriateness of the captured data for incorporation into future applications of the biosignature.

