		**Adherence metrics**									
			Hours of smartwatch wear, % complete of surveys and check-ins							✔	

^a^HRV: heart rate variability.

^b^6MWT: 6-minute walk test.

^c^PEG 3-item: Pain, Enjoyment of Life, and General Activity scale.

^d^CALI-9: Child Activity Limitations Interview.

^e^BPI-SF: Brief Pain Inventory – Short Form.

^f^PPST: Pediatric Pain Screening Tools.

^g^SF-MPQ-2: Short-Form McGill Pain Questionnaire-2.

^h^NRS: Numeric Rating Scale.

^i^PROMIS: Patient-Reported Outcomes Measurement Information System.

^j^PHQ-2: Patient Health Questionnaire-2 item.

^k^GAD-2: Generalized Anxiety Disorder-2 item.

^l^PANAS-10: Positive and Negative Affect Schedule.

^m^ASWS-SF: Adolescent Sleep Wake Scale–Short Form.

^n^Not a validated measure, adapted from NRS format (ie, “On a scale from 0 to 10, how would you rate your overall physical activity today?”)

^o^Available to complete unprompted, retrospectively or in real time, outside of time-based daily check-in

^p^TSST-OL: Trier Social Stress Test, online/remote.

^q^PANES: Physical Activity Neighborhood Environment Scale.

^r^mMOS-SS-8: 8-item modified Medical Outcomes Study Social Support Survey.

^s^ULS-8: 8-item UCLA Loneliness Scale.

^t^PSS-10: 10-item Perceived Stress Scale.

^u^CHIS: California Health Interview Survey.

^v^WHOQOL-2: World Health Organization Quality of Life-2.

^w^PCS-6: Pain Catastrophizing Scale-6 item.

^x^NIDA-2: Level 2—Substance Use—Child Age 11–17 instrument from the National Institute on Drug Abuse.

^y^PGIC: Patient Global Impression of Change.

^z^TFA: Theoretical Framework of Acceptability.

^aa^NPS: Net Promoter Score.

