The participants are instructed to wear the Apple Watch for at least 18 hours per day during the 12-week observation period. Apple Health Kit data are collected, uploaded, and stored through the third-party digital health and research platform. Metrics of interest include those related to respiratory function (eg, respiratory rate), heart activity (eg, heart rate, heart rate variability), physical activity (eg, steps, bouts of activity, standing time), sleep (eg, in-bed time, sleep phases), and mobility (eg, gait speed, walking asymmetry, step length) (Table 1). Survey completion rate and adherence to required watch wear times are monitored by the study team. Participants receive notifications from the study team to encourage high levels of adherence based on completion standards selected a priori (eg, number of daily check-ins completed each week and daily and nightly hours of wear). Participants receive weekly monetary incentives for completing each component of the study, with up to US $210 total. Those who do not meet adherence standards may not be eligible to receive a given week’s compensation. Furthermore, those consistently not meeting standards within the first few weeks of the study may be withdrawn in an effort to allocate research team time to adherent participants and prevent excessive amounts of missing data. At the end of the 12-week observation period, the participants complete an additional battery of discharge surveys, once again deployed through the third-party app (Table 1). They also complete a series of task-based measures prior to study discharge.

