### Task-Based Measures (Secondary)

#### Overview

The participants complete an additional stress task and a functional task to capture physiological responses to standardized challenges. These tasks are collected on a subset of the study cohort to examine responses to acute stressors. Although not required for the development of the initial biosignature, physiological responses and performance metrics related to these standardized challenge paradigms may improve the sensitivity of the biosignature in future iterations. Additionally, the results will provide unique insight into the pain experience by allowing for a standardized comparison across participants, supporting future hypothesis generation.

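### Acceptability feedback is described only at the end of the study, while non-adherent youth may be withdrawn early, so it will come mainly from completers

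*Protocol article*

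**What the plan says.** The Introduction of the protocol article sets the aim: "The secondary aim of this study is to assess the feasibility, acceptability, and appropriateness of the captured data", with a view to later use of the biosignature.

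Three places determine who supplies the feedback:

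- **Exit Interview.** "Following completion of the 12-week protocol, baseline and discharge surveys, TSST-OL, and 30s-STS, the participants are invited to complete a semistructured exit interview". The TFA and NPS are described directly afterwards, as part of the same step. The section says the feedback will inform ongoing procedures and guide Phase 2.
- **Table 1, Implementation outcomes.** The TFA, NPS and exit interview carry one tick each, which appears to fall in the discharge column (the table layout is damaged in the text available). No baseline, mid-study or withdrawal assessment is listed for them.
- **Smartwatch Metrics (Primary).** Of participants with poor adherence, it says that "those consistently not meeting standards within the first few weeks of the study may be withdrawn". The stated reason is "to allocate research team time to adherent participants and prevent excessive amounts of missing data".

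Two other statements bear on the point. The Overview under Task-Based Measures says of the stress test and the sit-to-stand task: "These tasks are collected on a subset of the study cohort to examine responses to acute stressors". Table 1 also lists adherence as an implementation outcome: "Hours of smartwatch wear, % complete of surveys and check-ins". According to Smartwatch Metrics, the team monitors survey completion and wear time.

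**The concern.** Acceptability is a judgement about burden: at least 18 hours of wear a day, daily check-ins for 12 weeks, and two recorded tasks. Failing to keep up with that burden is one sign that a participant finds it too heavy. The plan allows such participants to be removed early, and the only feedback it describes comes at the end. Being asked about acceptability therefore depends on behaviour that is probably related to the answer.

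This is a matter of data collection. If withdrawn youth never receive the TFA or NPS, no later analysis can recover their answers.

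The feedback is meant to guide Phase 2, another 12-week watch study, which will focus on youth experiencing health disparities. The Outcome Measures section itself notes differences in digital access and literacy among participants. Feedback mainly from those who managed the full protocol could miss the barriers that matter most there.

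The placement of the interview after both tasks adds a second problem. Read literally, it narrows the group again, to the subset that performs them.

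**Working it through.** **Figures in the plan.** The article gives no expected withdrawal rate, completion rate or acceptability threshold for this aim, so there is no figure to reproduce. The check has two parts: setting the sections side by side, and an illustration on assumed inputs.

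**Step 1: the path of a poor adherer.** A participant who repeatedly misses standards may be withdrawn in the opening weeks (Smartwatch Metrics). The interview, TFA and NPS are described after the 12 weeks (Exit Interview; Table 1). No section describes a feedback contact at withdrawal. Followed as written, this participant contributes adherence data up to exit but no acceptability data.

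**Step 2: the two task statements.** Overview: tasks in a subset. Exit Interview: the interview follows completion of both tasks. If the second is a condition, participants outside the subset are not interviewed. If it is only a typical sequence, the sentence does not say who is invited. The text does not settle which is meant.

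**Step 3: size of the overstatement (all inputs assumed).** Let c be the share who complete, A_c acceptability in completers and A_n acceptability in non-completers.

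- All-enrolled acceptability = c × A_c + (1 − c) × A_n
- Overstatement = (1 − c) × (A_c − A_n)

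With c = 0.80, A_c = 0.85 and A_n = 0.50: 0.80 × 0.85 + 0.20 × 0.50 = 0.78, so the overstatement is 0.20 × 0.35 = 7.0 points.

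With A_c held at 85%, the overstatement in points is:

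| Completion | A_n = 85% | A_n = 70% | A_n = 50% | A_n = 30% |
|---|---|---|---|---|
| 90% | 0 | 1.5 | 3.5 | 5.5 |
| 80% | 0 | 3.0 | 7.0 | 11.0 |
| 70% | 0 | 4.5 | 10.5 | 16.5 |
| 60% | 0 | 6.0 | 14.0 | 22.0 |

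**Step 4: bounds if nothing is known about non-completers.** The all-enrolled value lies between c × A_c and c × A_c + (1 − c). At 80% completion that is 0.68 to 0.88. The interval includes values above 85%, so the upward direction is expected but not proven.

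**Step 5: why the adherence denominator should be stated.** Assume 20% are withdrawn at week 3 after completing 25% of check-ins until then, and the rest complete 85%.

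- Retained participants only: 85%.
- All enrolled, days in the study only: (0.8 × 0.85 × 12 + 0.2 × 0.25 × 3) / (0.8 × 12 + 0.2 × 3) = 8.31 / 10.2 = 81.5%.
- All enrolled over all 12 weeks, later days counted as not completed: 0.8 × 0.85 + 0.2 × 0.25 × 3/12 = 69%.

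The same behaviour gives 85%, 81.5% or 69%, and most of the spread comes from how days after withdrawal are scored.

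**The case against.** The strongest reply is that the Exit Interview sentence gives a sequence and is not an eligibility rule. The TFA and NPS sentence states no condition of its own, and the subset wording in the Overview argues against a literal requirement to complete both tasks. Contact at withdrawal is an operational detail that the full protocol may contain. The aim has no acceptability threshold, and the main features of Phase 2 are already set out without reference to these results.

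Much of this stands. The article does not bar withdrawn youth from giving feedback, and the stakes are moderate. But it does fix the timing of feedback at the end, describes no other route, and permits early removal for poor adherence. A tilt toward completers follows from what it states.

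A reader might also infer three stronger things that the document does not support:

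- **That adherence is recorded only at discharge and so is lost for withdrawn youth.** Wear and survey completion are monitored during follow-up, and the withdrawal rule could not operate otherwise. The discharge tick plausibly marks when adherence is summarised.
- **That reported adherence is inflated by construction.** This would require withdrawn youth to leave the denominator. The article does not say so, and an article commonly leaves the denominator to the analysis plan.
- **That the biosignature loses the data of withdrawn youth.** No section says data before withdrawal are discarded, and Handling Missing Data provides for incomplete series.

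**Conclusion.** The point holds for acceptability. As described, the interview, TFA and NPS will come mainly from participants who reach the end, after a step that may remove those who struggle. Acceptability is expected to be overstated, on the assumption that non-completers find the study less acceptable than completers.

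The size cannot be established from the document. On the assumed grid above it runs from 0, if the groups agree, to 22 points at 60% completion with 85% against 30%.

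The Overview and Exit Interview sections are inconsistent about the tasks and must be reconciled. Feasibility measured by adherence is not shown to be biased; it only needs its denominator stated. This is a worthwhile improvement to a secondary aim and does not undermine the primary aim.

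**What to change.** 1. Send the TFA and NPS through the app to every enrolled participant at discharge or at withdrawal, whichever comes first, without making task completion a condition.
2. Offer withdrawn youth the exit interview.
3. Reconcile the Overview and Exit Interview sections, stating who is invited to the interview and whether either task is a precondition.
4. Report, beside the acceptability results, the response rate and the number withdrawn for non-adherence. Bounds as in step 4 of the working would show how much non-response could matter.
5. Report wear and check-in adherence over all enrolled participants, stating the denominator and how days after withdrawal are counted.

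The cost is one added survey trigger, a few more interviews and some extra reporting. Response among withdrawn youth will probably be low, so the change reduces the selection without removing it, and the figures may look less favourable. The article reports 190 enrolled of up to 500 at December 15, 2025, so up to 500 − 190 = 310 later participants could be covered from enrolment if the change were made from that point.

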#### Collaborations With People With Lived Experience

All aspects of this study were developed in partnership with people with lived experience, including patients, caregivers, and patient advocacy groups. These patient and advocacy partners were and continue to be involved in every aspect of the study, including grant preparation, development of recruitment materials, and selection of outcome measures. For example, based on feedback from patients and advocacy partners, the participant-facing app was modified to enable retrospective reporting of a pain flare, such as when a current pain flare is too severe to report in real time. Additionally, partner feedback prompted the research team to modify a short recruitment video that had previously focused on negative aspects of living with chronic MSK pain. The new video instead focuses on the positive impact and hope inspired by the study. Additionally, patient and advocacy partners noted that including daily visualizations of deterioration in smartwatch metrics via the app interface (eg, poor sleep, reduced activity) may exacerbate participant anxiety and hopelessness surrounding the likelihood of a pain flare. Based on this feedback, the study team modified the app interface to allow participants to hide unwanted data visualizations not required for the study. The participants can also opt out of any health app notifications or alerts for abnormal readings. Alternatively, the study team implemented positively framed visualizations and notifications through the visual tracking of smartwatch wear time goals and notifications for opportunities to implement participant-preferred wellness strategies. Importantly, patient and advocacy partners attended an in-person study launch meeting in December 2024 and continue to provide feedback on recruitment materials, outreach efforts, and research activities via virtual monthly team meetings.

### Analysis Plan

#### Outcome Measures

A digital biosignature will be developed to enable the detection of a change in pain status. The primary outcome used to validate the biosignature (ground truth) will be the participant’s self-reported onset of a pain flare. Additional models will be explored to predict secondary outcomes such as a clinically relevant change in pain interference, namely, 2 units on the Pain, Enjoyment of Life, and General Activity (PEG 3-item) scale or the onset of pain flares lasting for more than 2 days only. To improve pain flare prediction, participants may be stratified by demographic features known to impact the pain experience, and models may be adjusted using partial correlation. Accounting for individual factors may be particularly relevant when considering differences in digital access and literacy among participants residing across diverse geographic locations.

#### Data Reduction

Raw physiological signals (eg, heart activity, step counts, sleep stages) will be synchronized across modalities and aligned to a common timeline while preserving native sampling frequencies. To capture information across temporal scales, features will be engineered using a *multiresolution aggregation strategy*. For each signal, summary statistics will be computed over short windows (seconds to minutes) and further aggregated into intermediate (hourly) and daily summaries. All features derived at finer resolutions will be consolidated into a single daily feature vector, enabling the integration of short-term variability and longer-term physiological trends. The model prediction target and evaluation will be defined at a chosen time scale (eg, daily). Any windowing will only use past data relative to the prediction time to avoid leakage.

In addition to static summaries, *dynamic features* will be generated to characterize within-day temporal structure and behavior. These may include acceleration-based metrics (eg, mean acceleration), measures of temporal change (eg, slopes and rates of change), and circadian rhythm features. Complexity metrics (eg, entropy-based measures) may also be included to quantify signal regularity.

#### Handling Missing Data

Missing data due to nonwear or sensor dropout will be handled using a hierarchical approach. Short gaps will be interpolated when physiologically appropriate, whereas longer gaps will be left missing at the raw level. Daily features may be imputed using time-series–aware methods (eg, forward/backward filling within individuals). Missingness indicators will be included as additional covariates in model development to account for information loss.

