Participants enrolled in Phase 2 also have the opportunity to receive enhanced “wellness alerts,” which would be triggered by a deterioration in the pain experience as detected through abnormal smartwatch readings. The goal of these “wellness alerts” is to prompt users toward proactive self-management strategies (eg, pacing, sleep hygiene) in an effort to prevent or reduce the severity of the predicted pain flare. Patient and advocacy partners recommended positive framing of these “wellness alerts” (ie, opportunities for enhanced wellness strategies) as opposed to “pain flare predictions,” which may be negatively interpreted and lead to increased anxiety and hypervigilance. The accuracy of the enhanced “wellness alerts” will be assessed via comparison to self-reported pain flare onset through measures of accuracy, precision, and true positive and false negative rates. This “wellness alert” system is expected to empower patients by reducing feelings of helplessness surrounding unpredictable fluctuations in pain status. In addition, the alerts may serve as an additional tool to promote pain-related self-efficacy, which may serve as a protective factor in youth with chronic pain [45].

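### The imputation rule permits backward filling of missing daily features without the past-only limit set for windowing, so post-onset data can enter pre-onset predictors

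*Protocol article*

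**What the plan says.** The primary ground truth is "the participant’s self-reported onset of a pain flare" (Outcome Measures). Features are consolidated into one vector per day, and the target is set at a chosen time scale, with daily as the example (Data Reduction). The same section states the safeguard: "Any windowing will only use past data relative to the prediction time to avoid leakage".

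Handling Missing Data, the next section, has three parts:

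- Raw signals: "Short gaps will be interpolated when physiologically appropriate, whereas longer gaps will be left missing at the raw level".
- Daily values: "Daily features may be imputed using" time-series-aware methods, the example being "forward/backward filling within individuals".
- Flags: "Missingness indicators will be included as additional covariates in model development to account for information loss".

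None of the three is limited to data available at the prediction time. Model evaluation is split by participant (Sample Size Justification and Power Analysis). Phase 2 alerts are to be "triggered by a deterioration in the pain experience as detected through abnormal smartwatch readings" and are meant to precede the flare (Future Directions (Phase 2)).

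**The concern.** Backward filling gives a missing day the value of the next observed day. If the watch was off the day before a flare, the predictor for that day can take heart rate, sleep or step values recorded during the flare. A past-only window over the daily vectors does not help, because the later value already sits inside an earlier day.

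At stake is the main product of Phase 1: the performance estimates and the SHAP ranking of features. Both would be tilted towards features that change during a flare rather than before it. An alert system needs the latter. The backward-fill step also has no counterpart when an alert has to be issued, so Phase 1 performance obtained with it would not describe the system in use.

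**Working it through.** **1. The two rules side by side.** Let the prediction be made at the end of day *t*, for onset on day *t*+1. Data Reduction allows windowing over data up to *t*. Backward filling of a missing day *t* uses day *t*+1 or later. When the next observed day falls in a flare that began after *t*, the day-*t* predictor holds post-onset data. If the target is instead same-day detection, a value from a later day is still not past data.

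**2. Do the stated safeguards remove it?**
- Participant-level splits separate people. This leak runs over time within one person, so it is present in training and test folds alike.
- Missingness indicators mark a filled value but leave its content unchanged.
- Interpolation of a short raw gap leaks in the same way only if the gap spans the prediction time. This was not quantified.

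**3. Size.** The article states no flare rate, missing-data rate, feature shift or expected AUROC, so there is no figure of its own to reproduce. All inputs except the 12 weeks (84 days) and the sample size (up to 500; 400 as the 80% target) are assumptions:
- onset risk 7% to 8% per flare-free day
- mean flare length 3 days
- lag-1 autocorrelation 0.3
- 5% to 30% of days missing
- a feature with no pre-onset signal (true AUROC 0.50) that shifts by δ SD during a flare

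*Approximation.* With a fraction *m* of days missing at random and the next day observed, AUROC ≈ 0.5 + *m*·[Φ(δ/√2) − 0.5].
- *m* = 0.05, δ = 0.5: 0.5 + 0.05 × (0.638 − 0.5) = 0.507
- *m* = 0.20, δ = 1.0: 0.5 + 0.20 × (0.760 − 0.5) = 0.552
- *m* = 0.30, δ = 1.5: 0.5 + 0.30 × (0.856 − 0.5) = 0.607

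This runs somewhat high, because the next day may be missing too and the fill then reaches further ahead.

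*Simulation, AUROC for next-day onset over all flare-free days, backward-only fill:*

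| Days missing | δ = 0.5 | δ = 1.0 | δ = 1.5 |
|---|---|---|---|
| 5% | 0.506 | 0.512 | 0.516 |
| 20% | 0.524 | 0.546 | 0.56 to 0.57 |
| 30% | 0.534 | 0.565 | 0.59 |

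Other results:
- Forward fill only: about 0.50 throughout.
- Forward fill first, then backward fill for leading gaps only: within about 0.002 of forward fill.
- Pre-onset days missing twice as often as other days, 30% missing: backward-only fill gives 0.571 (δ = 0.5) and 0.633 (δ = 1.0).
- Filled days alone: about 0.62 to 0.65 (δ = 0.5) and 0.72 to 0.77 (δ = 1.0). These describe the imputed days, not the whole analysis.
- True pre-onset signal of 0.3 SD and δ = 1.0: complete data give 0.583, forward fill 0.541 to 0.578, backward fill 0.591 to 0.666. Backward fill beats complete data, which is possible only because it imports later information.
- No shift during flares: backward fill does not inflate.

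**The case against.** The article does not commit to backward filling. The wording is permissive and the method is given as an example. The past-only sentence literally governs windowing, and read by its purpose it could be taken to cover imputation as well. The order of filling is not stated. On one ordinary reading, forward first and backward only for leading gaps, the inflation all but disappears. Whole-day gaps may also be uncommon: Smartwatch Metrics (Primary) describes an instruction to wear the watch at least 18 hours a day, adherence notifications, weekly incentives and possible withdrawal of non-adherent participants. Finally, Phase 2 plans prospective validation in a new cohort.

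Most of this stands, and it limits the point to what the wording permits. It does not remove it. Backward filling is one half of the only example given, no order or limit is attached, and Phase 2 could expose optimism but would not correct the Phase 1 estimates or feature rankings.

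A reader might infer three stronger things that the document does not support:
- **That the plan breaks its own rule and its accuracy will be inflated.** The text supports only that leakage is permitted and that accuracy can be inflated.
- **That the model could not run in Phase 2.** Only the backward-fill step could not; a fitted model can still score complete or forward-filled days.
- **That the indicators make matters worse by teaching the model when to trust a leaked value.** No model with indicators was fitted, so this is untested.

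**Conclusion.** The point holds as a gap between two adjacent sections: the past-only safeguard is stated for windowing and not carried over to imputation, where a method that uses later data is named. If backward fill is applied to pre-onset gaps, it biases Phase 1 performance upward for any feature that changes during flares, and such features are what the study hopes to find.

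Under the assumptions above, a true AUROC of 0.50 becomes about 0.51 to 0.59 over all days, and more if pre-onset days are missing more often. With forward fill, or backward fill confined to leading gaps, there is practically no bias. The direction follows from the method; the size cannot be derived from the document. This should be fixed, but it is not fatal: the study is a model-development cohort without a hypothesis test, and prospective validation is planned.

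**What to change.** In Handling Missing Data, remove backward filling from the primary analysis, or keep it only as a labelled sensitivity analysis. Extend the Data Reduction rule with one sentence: all imputation and interpolation of predictors use only data available at or before the prediction time, and days that cannot be filled this way stay missing with their indicator.

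The cost is a sentence in the plan and a pipeline setting. Slightly more days stay missing, and the reported AUROC may be lower. Data collection and analysis are ongoing, so the change is best made before any performance result is reported.
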